### Data Collection, Management, and Security

Interviewers are trained in the standard administration of the instruments and handling of distressed parents or volunteers. The research team meets at least monthly to review interview techniques and ensure consistency of administration. All data are checked to ensure accuracy and consistency of data entry.

Family participants will complete a survey every 3 months for 15 months, commencing at recruitment and continuing until 15 months post their own recruitment date. The baseline and follow-up surveys will be collected by a research assistant (at the home of the participant or over the phone) or self-completed by participants if preferred. Surveys can be completed on a paper form or a word document sent via email, or they can be Web based using Qualtrics software (Qualtrics, Provo, UT). The Web-based version of the survey has been tested for usability and technical issues in one of the study sites and will eventually be rolled out to all sites. Previous research suggests that offering multiple survey response modes allows participants to choose what is most convenient for them, with little negative impact on data quality [50]. The use of iPads and Web-based survey software has been shown in the previous research to increase efficiency and reliability and to reduce data entry errors [51-53]. All data collected via paper or emailed word documents will be entered into the Web-based survey by a research assistant. Data will be stored in a password-protected Qualtrics database and backed up to a password-protected folder on a server. Only members of the research team will have access to the data.

The Web-based survey will be administered in two sections. Section A includes prefilled items (eg, demographic questions, breastfeeding status, service expectations) for the participant to update (if applicable), and Section B contains all other items. Section A requires a link to be manually generated for each participant at each time point. Section B uses a generic link to the respective time point. For participants self-completing, both Section A and Section B links will be manually emailed by research assistants in each site and reminders (emails, text messages, or phone calls) will be sent weekly until the survey is completed or for 6 weeks post the due date for the survey. Both sections require the participant to enter a unique identifying number at the start of the survey. Where duplicate entries occur, the earliest completed response will be retained.

Items will always be presented in the same order, and adaptive questioning will be used to only display relevant questions to participants. Dependent on adaptive questioning, Section A has a minimum of twelve pages and a maximum of forty-five pages, with a maximum of eight questions per page. Dependent on adaptive questioning, Section B has a minimum of forty-three pages and a maximum of seventy-eight pages, with a maximum of six questions per page. Multiple-choice questions use forced choice validation, with an option of “refused” on all questions. Open-field responses use requested response validation, with a prompt appearing before the survey can be progressed to the next page. A back button will be available to the respondents; however, there is no provision to review the completed survey before submission.

Volunteers and comparison group members can opt to complete their surveys over the telephone with a research assistant who enters their response into the Web-based survey using an iPad, independently using a paper survey that is mailed to them, or Web based using Qualtrics.

All data are stored on password-protected computers at Macquarie University and at Western Sydney University, to which only the research team has access. Data are de-identified during data entry, at which time all names are replaced with participant numbers. Data are stored in accordance with the requirements of the Australian National Health and Medical Research Council and the Privacy Act 1988.

### Data Analysis

#### Quantitative Analysis

Primary and secondary outcomes will be extracted and analyses conducted using SPSS Version 25.0. Analysis will be completed both on an intention-to-treat and a per-protocol basis. Families will be considered to have received the scheduled dose if they receive visits from the volunteer for at least 3 months with no gap between visits of more than 2 weeks. Volunteer outcomes will be analyzed using cross-sectional comparative analysis. Participant demographic data will be analyzed using basic descriptive statistics. Prior to the analysis of outcome measures, data will be assessed for outliers and normality. Scale variables will be analyzed using independent *t* test or analysis of variance or their nonparametric counterparts (eg, Mann–Whitney U test) if appropriate. Mixed modeling will be completed on the primary and secondary family outcomes to assess the effect of the intervention over time while adjusting for possible confounders. Categorical variables will be analyzed using odd ratios or chi-square analysis. For all analyses, two-tailed tests will be undertaken: findings with α<0.05 will be determined to be statistically significant. ESs will be calculated for all trends (α<0.1) and statistically significant findings; (ES≈0.5 [Cohen *d*]) will be considered clinically meaningful. Overall, the program will be considered to have been effective if at least one of the primary outcomes is positive and the other is neutral.

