**Methods:**

The RCT is being conducted in 7 sites across Australia. We aim to recruit 300 families to the study: 150 control (services as usual) and 150 intervention (services as usual + volunteer home visiting) families. Intervention families will receive the service for 3-12 months according to their needs, and all participants will complete 6 data collection points over 15 months. A minimum of 80 volunteers will also be recruited, along with a matched community comparison group. The volunteers will complete 3 data collection points over 12 months. Primary outcomes include community connectedness and parenting competence. Secondary outcomes include parent physical and mental health; general parent well-being; parent empowerment; the child-parent relationship; sustainability of family routines; child immunization; child nutrition or breastfeeding; number of accidental injury reports; and volunteer health, well-being, and community connectedness.

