### Secondary Research Questions

Do differences exist in the patterns of parent health, well-being, and empowerment and the sustainability of family routines over time between those who receive the Volunteer Family Connect program and those in the services as usual control group?Does volunteer home visiting lead to differing outcomes for children aged 0-5 years in intervention families compared with those in control group families on measures of immunization, breastfeeding duration, nutrition, and accidental injury?Do different patterns of outcomes for intervention families depend on the location (ie, availability and accessibility of health, welfare, and early childhood services in the local area) and the duration of the program (ranging from 3 to 12 months)?Does volunteering on the Volunteer Family Connect program lead to differing outcomes on measures of well-being, health, community connectedness, and self-efficacy for volunteers over time compared with a matched community comparison group?

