### Participants

#### Eligibility Criteria

Eligible families will be those who meet the following criteria: (1) families having one or more children in the 0-5 age range; (2) families at risk of geographic or social isolation (eg, separated from usual support networks due to immigration); (3) parents seeking to develop confidence and increase their parenting knowledge and skills; (4) families residing in the specified service area; and (5) families unable to resource or access other support services (eg, due to financial hardship). Language translation services have been secured so that families with a first language other than English will not be excluded from participating in the research.

Families will be ineligible for the study if any of the following conditions apply: (1) there is active abuse or domestic violence within the family; (2) there is unmanaged mental illness within the family; (3) substance abuse is an issue within the family; (4) the family is living in an environment unsafe for the volunteer to visit; and (5) the family is under child protection orders or there are unsettled parenting arrangements. Families referred for volunteer home visiting will be assessed for eligibility by the local Volunteer Family Connect program coordinator according to the usual practice, and referrals will be made to other services within the community if the family is ineligible.

All current volunteers within the Volunteer Family Connect program will be invited to participate in the study. It is not possible to examine outcomes for volunteers employing a randomized controlled trial (RCT) design because this would halve the number of volunteers available and significantly impact program implementation. Instead, a community comparison sample will be recruited that will be matched on age, gender, education and employment levels, and geographical location.

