#### Participant Timeline

Data collection spans a 15-month period so that there is at least one data collection point post family exit from the Volunteer Family Connect program (families receive the program for 3-12 months depending on their support needs). Volunteer outcomes will be measured over a 12-month period at 6-month intervals.

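### The volunteer comparison is fixed as cross-sectional, although the question is about outcomes over time in non-randomized groups measured three times

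*Protocol article*

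**What the plan says.** All references are to the protocol article.

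- **Question.** Secondary Research Questions: "Does volunteering on the Volunteer Family Connect program lead to differing outcomes on measures of well-being, health, community connectedness" and, to finish the list, "self-efficacy for volunteers over time compared with a matched community comparison group". The wording is both causal and longitudinal.
- **Data.** Participant Timeline: "Volunteer outcomes will be measured over a 12-month period at 6-month intervals". The abstract agrees: "The volunteers will complete 3 data collection points over 12 months". The volunteer rows of Table 1 mark enrollment, month 6 and month 12.
- **Design.** Eligibility Criteria: "It is not possible to examine outcomes for volunteers employing a randomized controlled trial (RCT) design". A community sample is used instead, matched on age, gender, education, employment and location. The same section says: "All current volunteers within the Volunteer Family Connect program will be invited to participate in the study". Under Recruitment, comparators come from volunteers' non-volunteering acquaintances or from Facebook advertising.
- **Size.** Sample Size gives 80 volunteers and 80 comparators, reflecting current volunteer numbers. No power statement is made for this comparison.
- **Analysis.** Quantitative Analysis: "Volunteer outcomes will be analyzed using cross-sectional comparative analysis". The same paragraph names mixed modeling over time, with adjustment for confounders, for the family outcomes only.

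**The concern.** The stated method does not answer the stated question. Comparing two groups at a point in time describes a difference in level. It does not show whether the groups moved apart over the 12 months, although the data to show this are being collected.

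The choice matters more here than it would in a randomized comparison. The matching variables do not include health, connectedness or self-efficacy, which are the outcomes being measured. People who take up volunteering may differ on these from people who do not, and a cross-sectional contrast cannot separate such a difference from an effect of volunteering. The plan gives the longitudinal, confounder-adjusted model to the randomized family comparison and withholds it from the comparison that lacks randomization.

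Volunteer benefit is a visible aim. The abstract's Objective presents the study as the first to examine outcomes for both families and volunteers, and the Introduction makes volunteers' well-being and social connection a program aim and says the results can inform public policy.

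**Working it through.** The plan gives no power or effect-size figure for the volunteer comparison, so there is none to reproduce. The following shows how a residual difference would pass through the stated method.

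**Inputs from the protocol:** 80 per group (Sample Size); two-sided α = 0.05 and a meaningful effect of about d = 0.5 (Quantitative Analysis).

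**Assumptions:** no effect of volunteering; outcome SD = 1; a stable residual difference d after matching, taken over a range because the documents give no value; no attrition.

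**1. Standard error of a cross-sectional difference.** SE = √(2/80) = 0.158 SD.

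**2. Chance of p<0.05 with no effect of volunteering.** P = Φ(d/SE − 1.96) + Φ(−d/SE − 1.96).

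| Assumed residual d | d/SE | Chance of p<0.05 |
|---|---|---|
| 0 | 0 | 5% |
| 0.1 | 0.63 | 10% |
| 0.2 | 1.26 | 24% |
| 0.3 | 1.90 | 48% |
| 0.5 | 3.16 | 89% |

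The expected estimate equals d itself, so a residual of 0.5 SD would reach the plan's own threshold for a clinically meaningful effect. For scale, the smallest difference detectable with 80% power is (1.96 + 0.84) × 0.158 = 0.44 SD.

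**3. Alternatives that use baseline.** A simulation had 3,000 runs per scenario, three waves, assumed within-person correlation of 0.5 or 0.7, and no effect of volunteering:

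- Change from baseline to month 12: mean estimate about 0 and about 4–6% significant, for residual differences of 0, 0.2, 0.3 and 0.5 SD.
- Month-12 score adjusted for baseline (ANCOVA): mean estimate 0.06–0.10 at d = 0.2, 0.09–0.15 at 0.3 and 0.15–0.25 at 0.5, with 8–10%, 11–19% and 25–42% significant. In non-randomized groups this reduces the bias without removing it.

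**4. Precision of the change contrast.** Relative to a single-wave comparison its variance factor is 2(1 − r). At r = 0.6 this is 2 × 0.4 = 0.80, a 20% reduction. At r = 0.5 it is 1.00, and below 0.5 precision is lost.

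**The case against.** The strongest counter-argument concerns the baseline. Participants are current volunteers, so their first measurement is already post-exposure. Change from that point subtracts benefit gained before enrollment along with any selection difference. A program that helped volunteers early and then plateaued would show a change near zero. The level difference is the only contrast that includes earlier benefit, though it is confounded. This stands: neither contrast estimates the effect of starting to volunteer. It is a reason to report both with clear labels, and it does not rescue a cross-sectional analysis as the answer to a question about outcomes over time.

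It can also be said that the component is secondary and openly non-randomized, and that matching will remove some confounding. Both are true and limit the weight of the point. If cross-sectional means a comparison at each wave, the three results still give no test of difference in change.

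Three stronger readings are tempting, and the documents do not support them:

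- A reader might infer that pre-existing differences will be reported as effects of volunteering. Only what remains after matching can be, and its size and direction are unknown.
- A reader might infer that the analysis discards a pair matching. The protocol says the sample is matched on certain characteristics, not that individuals are paired.
- A reader might expect using baseline to cut variance by 36% at a correlation of 0.6 (1 − 0.6²). That is the ANCOVA figure. The change contrast gives 20%.

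**Conclusion.** The point holds as a contradiction within the stated text. The question is longitudinal, the data are longitudinal and the groups are not randomized, yet the one method named for volunteers is cross-sectional. An analysis plan would have to reverse that sentence, because adding detail to it would not be enough.

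Followed as written, the method does not estimate difference in change and carries any stable residual difference into the result in full. The false-positive chance runs from 5% with no residual to 89% at 0.5 SD. This range rests on 80 per group, no attrition and assumed residuals, so it shows sensitivity and does not predict what will happen. The case rests on bias; the gain in precision is modest and depends on the within-person correlation. The primary family comparison is unaffected.

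**What to change.** Replace the cross-sectional sentence with a repeated-measures mixed model on the three waves:

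- Fixed effects for group, visit and group-by-visit, with the matching variables as covariates.
- A participant-level random effect or a within-person covariance structure. Add a pair or set term only if matching was individual.
- The group difference in change from baseline to 12 months as the main longitudinal estimate, with between-group levels at each wave alongside it as descriptive.
- A statement that volunteers were already active at baseline, so the estimate reflects further change over 12 months and may miss benefit already gained. Word conclusions as association.
- If volunteering start dates are available, describe recent starters separately, among volunteers only. Prior volunteering time should not be a covariate in the two-group model, because it is zero or undefined for comparators.

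The cost is a change of analysis wording, with no new outcome data or visits. The protocol does not say whether start dates are recorded, so that item may need a small extra collection. The downsides are the post-exposure baseline and a loss of precision if the within-person correlation is below 0.5.

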#### Recruitment

Family participants will largely be identified through the Volunteer Family Connect usual service referral networks, which include child and family health nurses, general practitioners, or family support workers. The Volunteer Family Connect program is advertised within the community, and parents are welcome to self-refer to the program. If eligible for the program, families will be invited to speak to a member of the research team and, if interested, informed consent for the research will be secured. The family will then be randomly allocated by the research manager using computer-generated random numbers to receive either the volunteer home visiting program in addition to usual care services (Intervention group = Volunteer Family Connect + usual care services) or the usual care services only (Control group = usual care services).

The procedure used to recruit and allocate families is summarized in Figure 2.

An invitation will be extended to all volunteers currently involved with the 7 participating sites to participate in the research. The matched community comparison sample will be recruited via one of the following two strategies: (1) volunteers will be asked to pass on an invitation to participate in the research to nonvolunteering acquaintances in their local networks and (2) the research will be advertised through Facebook, targeting the local areas in which the Volunteer Family Connect program is being trialed.

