**Figure 2 figure2:**
[figure not shown]
Participant flow diagram.

The families will participate in data collection for a period of 15 months. Strategies have been put in place to support and encourage the retention of participants, including asking all participating parents to provide the name and phone number of a relative or friend who can be contacted by the researchers if we struggle to reach them; providing families with the contact details of the research team and asking them to advise us if their contact details change; providing each family with an Aus $20 gift voucher for a popular grocery store chain at each data collection point and sending thank you notes; and employing project offices who have strengths in the building of rapport with families. The decision to employ these strategies was primarily based on the positive experiences of the research team in the previous research projects [34,35].

A total of 80 volunteers and 80 comparison group members will be recruited to the study, reflecting current volunteer numbers.

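### The non-randomized volunteer comparison is matched on five factors, but its stated analysis neither uses the matching nor adjusts for those factors: a modest loss of precision, and residual imbalance left uncorrected

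*Protocol article*

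**What the plan says.** On design, the protocol article (Eligibility Criteria) states: "It is not possible to examine outcomes for volunteers employing a randomized controlled trial (RCT) design". Instead, "a community comparison sample will be recruited that will be matched on age, gender, education and employment levels, and geographical location". Under Recruitment, comparators come by two routes. In one, "volunteers will be asked to pass on an invitation to participate in the research to nonvolunteering acquaintances in their local networks"; the other is Facebook advertising aimed at the trial areas. Sample Size gives the numbers: "A total of 80 volunteers and 80 comparison group members will be recruited to the study, reflecting current volunteer numbers". Volunteers and comparators are measured at baseline, 6 and 12 months (Participant Timeline and Table 1), and the fourth secondary research question asks about their outcomes over time.

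On analysis, Quantitative Analysis assigns volunteer outcomes to a cross-sectional comparison. The sentence on tests reads: "Scale variables will be analyzed using independent *t* test or analysis of variance or their nonparametric counterparts", with the Mann–Whitney test as the example of the last. Categorical variables go to odds ratios or chi-square tests. Adjustment for possible confounders appears once, with a limited scope: "Mixed modeling will be completed on the primary and secondary family outcomes". No matching factor, pair identifier or baseline value is named for the volunteer analysis.

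**The concern.** The article gives confounder adjustment to the randomized comparison, which needs it least, and names none for the comparison that is not randomized. Two separate things follow.

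The first is precision. Matching makes the two groups alike on the matching factors, so the difference in means varies less from sample to sample than it would for two unrelated samples. An independent-samples test does not credit this: variance explained by the factors stays in its error term. Intervals come out too wide and p values too large, and power is lost.

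The second is bias. Forwarded invitations and Facebook advertising are convenience routes and may not deliver close matches on five factors. Dropout may also differ between groups in a way related to those factors. An unadjusted test corrects neither. The volunteer comparison is the only answer to the fourth secondary question, and the article presents the trial as the first to examine outcomes for both families and volunteers.

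**Working it through.** The article gives no power, standard error or detectable difference for the volunteer study, so there is no stated figure to reproduce.

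**Inputs from the article.** n = 80 per group (Sample Size); two-sided 0.05 (Quantitative Analysis); five matching factors (Eligibility Criteria).

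**Input assumed.** Share of outcome variance explained by the matching factors, ρ = 0.1, 0.2 or 0.3. Under exact one-to-one matching this is also the within-pair correlation that the factors produce. Outcomes are in SD units.

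**Formulas.**
- Standard error used by the independent test: √(2/80) = 0.158.
- True standard error under matching: √(2(1−ρ)/80).
- Ratio: 1/√(1−ρ).
- True error rate of the independent test: 2[1 − Φ(1.96/√(1−ρ))].
- Difference detectable at 80% power: (1.96 + 0.842) × standard error. Without matching, 2.802 × 0.158 = 0.443.

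| ρ (assumed) | True SE | SE ratio | True error rate | Detectable, matching ignored (nominal) | Detectable, matching used |
|---|---|---|---|---|---|
| 0.1 | 0.150 | 1.054 | 0.039 | 0.44 SD | 0.42 SD |
| 0.2 | 0.141 | 1.118 | 0.028 | 0.44 SD | 0.40 SD |
| 0.3 | 0.132 | 1.195 | 0.019 | 0.44 SD | 0.37 SD |

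The 0.44 is what the unmatched formula gives. In a matched sample the independent test does slightly better, because only its critical value uses the inflated standard error: 1.96 × 0.158 + 0.842 × true SE = 0.436, 0.429 and 0.421 SD. The gain from using the matching is therefore a little smaller than the table's last two columns suggest.

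**Power.** At 0.5 SD, the effect size the article treats as clinically meaningful, with ρ = 0.2 and 80 per group, simulated power is 90.7% with the independent test and 93.6% with a paired test, a gain of about 3 points. At 0.3 SD the normal approximation gives 47% against 52%, 56% and 62% for ρ = 0.1, 0.2 and 0.3.

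**Pair or group matching.** A simulation (6,000 runs per setting, one matching variable balanced exactly) compared the two forms. Without dropout, the SE ratio was 1.04 to 1.06, 1.13 to 1.14, and 1.19 to 1.20 at 10%, 20% and 30% explained variance. The true error rate was about 0.038, 0.027 to 0.028, and 0.020 to 0.022. The form of matching made almost no difference.

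**Random dropout, 20% per group (assumed).** 80 × 0.8 = 64 remain per group. If matching were one-to-one, 80 × 0.8² = 51 pairs would stay intact and 64 − 51 = 13 per group would lose their counterpart. The imbalance on the matching variable then averages zero, with an SD of about 0.08, and the estimate shows no mean bias.

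**Dropout related to a matching factor (assumed).** Comparator retention follows a logistic curve with slope 0.7 per SD of the matching variable; volunteers drop out at random. The groups end about 0.13 SD apart on that variable. The expected bias is √ρ × 0.128 = 0.040, 0.057 and 0.070 SD; the simulated bias was 0.04 to 0.07 SD. Adding the variable as a covariate brought it to about 0.005 SD or less. The false-positive rate of the unadjusted test stayed at 0.039 to 0.049, because the oversized standard error offsets the small bias. The same arithmetic applies to imperfect matching: a mismatch of m SD biases the estimate by √ρ × m.

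**The case against.** The strongest reply is that the error is conservative. Ignoring matching does not by itself bias the estimate, and it holds false positives below 5%, so no false claim of volunteer benefit arises from it. At 0.5 SD with all 80 per group, the power at stake at ρ = 0.2 is about 3 points. This stands, and it limits the weight of the precision argument.

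The text is also looser than it first looks. The sentence on tests is a general list for all scale variables, an analysis of variance could carry blocking factors, and the Discussion describes the volunteer work as a separate matched comparison study that may have a fuller plan. This stands only in part. The article names methods, says nothing of blocking or covariates, and names the adjusted model for family outcomes alone. That is a stated choice as well as an omitted detail.

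Three stronger readings are tempting, and the documents support none of them.

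- A reader might infer one-to-one pairs from the 80 and 80 and from the use of acquaintances. The article speaks only of a matched sample or group, and Facebook recruitment fits group-level matching at least as well.
- A reader might assume a strong within-pair correlation, such as 0.5, which would make the standard error 41% too wide. Nothing in the article supports that value. Under group matching it would require five demographic factors to explain half the outcome variance.
- A reader might infer that imbalance necessarily returns once participants drop out, or carry the families' planned retention (100 of 150) over to the volunteers. Random dropout causes no mean bias, and the article states no volunteer attrition. Treating two-thirds retention as 53 intact pairs would also require both members to leave together; independent dropout would leave 80 × (2/3)² ≈ 36.

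**Conclusion.** The point holds in a limited form. A non-randomized comparison, with matching as its only stated protection against confounding, is assigned an analysis that neither uses the matching nor adjusts for the factors behind it.

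The certain part is the direction: if the matching factors predict outcome, the stated tests are too conservative. Its size is modest and rests on an assumed explained variance of 10% to 30% and on close matching; looser matching would shrink it. The conditional part is bias. It arises only if matching is imperfect or dropout is related to a matching factor, and the 0.04 to 0.07 SD comes from one assumed scenario. The conclusion does not depend on whether matching is by pair or by group. It is worth correcting because a better analysis costs almost nothing.

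**What to change.** In Quantitative Analysis, state that volunteer scale outcomes will be analyzed by regression or a linear mixed model with the five matching factors (age, gender, education, employment, location) as covariates. For outcomes at 6 and 12 months, include the baseline value, which is already collected. Since current volunteers are invited, their baseline may already reflect volunteering, so say that the baseline-adjusted result concerns differences arising during follow-up. Add a random intercept for the pair only if matching is one-to-one, and state which form of matching is used. Use logistic regression with the same factors for categorical outcomes. Keep participants whose counterpart is lost; a simple paired test would discard them.

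The cost is a few sentences, a few degrees of freedom and, if matching is one-to-one, a pair identifier in the data file. The matching factors have to be recorded anyway to carry out the matching. No new participants or measurements are needed.
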